## Abstract

**Background:**

Older adults (> 65 years) with multiple chronic conditions (MCC) and depressive symptoms experience frequent transitions between hospital and home. Care transitions for this population are often poorly coordinated and fragmented, resulting in increased readmission rates, adverse medical events, decreased patient satisfaction and safety, and increased caregiver burden. There is a dearth of evidence on best practices in the provision of transitional care for older adults with MCC and depressive symptoms transitioning from hospital-to-home. This paper presents a protocol for a two-armed, multi-site pragmatic effectiveness-implementation trial of Community Assets Supporting Transitions (CAST), an evidence-informed nurse-led six-month intervention that supports older adults with MCC and depressive symptoms transitioning from hospital-to-home. The Collaborative Intervention Planning Framework is being used to engage patients and other key stakeholders in the implementation and evaluation of the intervention and planning for intervention scale-up to other communities.

**Methods:**

Participants will be considered eligible if they are > 65 years, planned for discharged from hospital to the community in three Ontario locations, self-report at least two chronic conditions, and screen positive for depressive symptoms. A total of 216 eligible and consenting participants will be randomly assigned to the control (usual care) or intervention (CAST) arm. The intervention consists of tailored care delivery comprising in-home visits, telephone follow-up and system navigation support. The primary measure of effectiveness is mental health functioning of the older adult participant. Secondary outcomes include changes in physical functioning, depressive symptoms, anxiety, perceived social support, patient experience, and health and social service use and cost, from baseline to 6- and 12-months. Caregivers will be assessed for caregiver strain, depressive symptoms, anxiety, health-related quality of life, and health and social service use and costs. Descriptive and qualitative data from older adult and caregiver participants, and the nurse interventionists will be used to examine implementation of the intervention, how the intervention is adapted within each study region, and its potential for sustainability and scalability to other jurisdictions.

**Discussion:**

A nurse-led transitional care strategy may provide a feasible and effective means for improving health outcomes and patient/caregiver experience and reduce service use and costs in this vulnerable population.

**Trial registration:**

# NCT03157999.

Registration Date: April 4, 2017.

## Background

Transitioning (moving) between hospital and home after a hospital admission can be a stressful and confusing time for patients and their caregivers. By necessity, the transition from hospital to home involves several professionals within and between disciplines and settings, all sharing the responsibility of care for an individual [1]. This results in numerous challenges to providing comprehensive and coordinated care, particularly for older adults (> 65 years) with multiple (> 2) chronic conditions (MCC) and depressive symptoms who experience frequent hospital-to-home transitions [2]. Care transitions for this population are often poorly coordinated and fragmented, resulting in increased readmission rates, adverse medical events, decreased patient satisfaction and safety, and increased caregiver burden [3–5].

These adverse outcomes have been attributed to factors such as lack of patient knowledge about available community-based services resulting in suboptimal or delayed utilization of these services [6], conflicting plans and instructions from different providers [7–10], medication errors [11, 12], lack of support for self-management of their complex chronic conditions [11, 12], lack of support for family caregivers, lack of communication and connections between older adults and health care providers, and untreated or under-treated depressive symptoms [13–15]. Factors related to social and structural determinants of health can further worsen the challenge of managing hospital to home transitions for older adults with MCC and depressive symptoms [16]. This is especially true for older adults with lower socioeconomic status, ethnocultural minorities, or persons living in rural or remote communities [17]. The consequences of poorly executed transitions are far reaching, leading to unnecessary costs to the health care system, and increased stress and burden on older adults with MCC and depressive symptoms and their caregivers. As the population of older adults increases, the number of persons living with MCC is expected to increase. Older adults with MCC are more likely to experience depressive symptoms than older adults without MCC (18). These data highlight the need for new, integrated healthcare delivery models to improve the quality and experience of hospital to home transitions for this vulnerable population.

Transitional care interventions have been recommended to address adverse outcomes in community-living older adults with complex needs transitioning from hospital to home [18–25]. The aim of transitional care is to ensure the coordination and continuity of health care when older adults move across care settings. Improvements in transitional care will simultaneously lead toward more integrated care, by bringing together services, providers, and organizations from across care settings and sectors; ensuring that services are coordinated and complement one another; and sharing information between providers accurately and promptly [1]. The goal is to develop a seamless unified system to ensure continuity of care for older adults managing MCC and depressive symptoms.

Although these Transitional Care Interventions have been linked to several positive outcomes, including decreasing hospital readmissions, the effectiveness of these interventions for older adults with MCC and depressive symptoms is uncertain. Most trials assessing the impact of transitional care interventions have excluded older adults with MCC, omitted mental health considerations such as depressive symptoms, provide little information on cost and implementation strategies, and used weak study designs [26–29]. Most of these studies have focused on acute care readmission rates as the primary measure of effect for many transitional care interventions, with limited attention to patient-relevant outcomes, such as health-related quality of life. Moreover, little is known about how, and within which contexts, care transition interventions and their components are effective. There is a need for evidence-informed best practices on transitional care for older adults with MCC and depressive symptoms since older adults with depression experience persistent health inequities that often lead to negative outcomes, such as reduced health-related quality of life, and high use of healthcare services [30–34].

### CAST study objectives

Our team designed a new hospital-to-home transitional care intervention to address these gaps in knowledge. The Community Assets Supporting Transitions (CAST) is a 6-month tailored patient-and caregiver-centred intervention delivered by a Care Transition Coordinator (CTC) who is a Registered Nurse (RN). The CAST intervention was designed to improve the quality and experience of hospital-to-home transitions by supporting families and caregivers and fostering collaborations between primary care and other interdisciplinary service providers, both within and outside of the health sector, in delivering home and community services. The study builds upon the results of our feasibility study that demonstrated that a 6-month nurse-led mental health promotion intervention for older home care clients with MCC and depressive symptoms, was feasible to implement and resulted in a statistically significant reduction in depressive symptoms, and a significant improvement in mental health and physical functioning [18]. Statistically significant reductions were observed in the use of hospitalization, ambulance service utilization and emergency room visits [18]. The intervention components (home visits, telephone contacts, care coordination) in the feasibility study are comparable to those featured in effective care transitions interventions [35–37]. The purpose of this paper is to provide a detailed description of the CAST study protocol and discuss any anticipated challenges to implementation and how these will be addressed.

### Research questions

The study addresses three research questions:
What is the effect of a new, nurse-led hospital-to-home transitional care intervention compared to usual care on health outcomes and costs for older adults with MCC and depressive symptoms and their caregivers?How is the new care transition intervention adapted and implemented in diverse settings?What is required to sustain and scale up the intervention?

It is hypothesized that, compared to usual care, the intervention will result in improvements in health outcomes for older adults with MCC and depressive symptoms while reducing the utilization of expensive healthcare services (e.g., hospitalization).

### Trial design

The research questions are being addressed using a pragmatic randomized controlled trial (RCT), which applies RCT methodology in actual care settings to better inform decisions about the probable benefits, harms and costs of real-world implementation [38, 39]. The design is further classified as a Type II hybrid effectiveness implementation study, which assigns equal weight to assessing program effectiveness and implementation [40, 41]. Hybrid designs are thought to facilitate the transition from research to practice and result in more rapid uptake of effective interventions [40, 41].

## Methods/design

The CONSORT Standardized Protocol Items: Recommendations for Interventional Trials (SPIRIT) [42] was used to structure the description of the CAST Trial presented in this manuscript and ensure that all relevant information is included. The participant timeline recommended by SPIRIT (42) shows the schedule of enrollment, interventions, and assessments (see Fig. 1) and these are all discussed in greater detail below.

**Fig. 1 Fig1:**
[figure not shown]
Standard Protocol Items: Recommendations for Interventional Trials (SPIRIT) Checklist: schedule of enrollment, interventions, and assessments)

### Study setting

The study is taking place in three distinct communities within the catchment areas of two Regional Health Authorities in Ontario. These three communities were selected because they are diverse with respect to geography (rural/urban), socio-economic, language, and ethno-cultural characteristics. A description of each of the three communities, along with relevant health status indicators, is provided below.

#### Site one

The North East Local Health Integration Network is one of Ontario’s geographically largest LHINs, comprising 44% of Ontario’s land mass and serving over half a million residents [43]. This area of Ontario has the largest Francophone population of any LHIN region and has 41 First Nations and 19 urban and rural aboriginal communities [43]. The North East LHIN has the second highest proportion of older adults (65+) in Ontario (LHIN: 20.4% vs. ON: 16.4%), and the second highest proportion of residents aged 75+ (LHIN: 8.9% vs. ON: 7.2%) [44]. The prevalence rates of North East LHIN residents with a self-reported chronic condition (LHIN: 49.3 per 100 vs. ON: 39.6 per 100) or classified as having multiple chronic conditions (LHIN: 22.2 per 100 vs. ON: 16.2 per 100) are higher than the prevalence rates for Ontario [44]. In 2015–16, a significantly lower proportion of North East LHIN residents reported having very good or excellent self-perceived health compared with Ontarians as a whole (LHIN: 56% vs. ON: 61%); the proportion of North East LHIN residents reporting very good or excellent self-perceived mental health was also significantly lower than that of Ontarians (LHIN: 66% vs. ON: 71%) [44].

#### Site two

The Hamilton Niagara Haldimand Brant (HNHB) LHIN is a population dense region of Ontario with 1.4 million residents [45]. The HNHB LHIN serves more than 260,000 older adults (65+ years) and is projected to increase by 35% by 2025 [46]. The HNHB LHIN has significant socio-economic diversity across the six communities within its catchment area [46]. One of the communities, the second site for the study, reports higher rates of high blood pressure (LHIN: 14.5% vs. ON: 12.9%) and arthritis (LHIN: 20.5% vs. 17.7%) compared to the provincial average [47]. This community reports a lower than provincial average of residents in low-income (LHIN: 7.6% vs. ON: 13.8%), and the highest number of primary care physicians per 10,000 population in comparison with other five communities within the HNHB LHIN (LHIN range: 4.7 to 6.5) [47].

#### Site three

The third site of the study is also within the catchment area of the HNHB LHIN. This community has a greater population than site two and a greater proportion of older adults (24.5%), with 15.7% of those residents living below the low-income threshold [47]. The community also has the second highest rate of older adults living alone and the highest percentage of repeat, unscheduled emergency department visits within 30 days for mental health conditions within the HNHB sub regions (21.2%), similar to the Ontario proportion [47]. This large community, although geographically similar to the second site, reports a lower than average socio-economic status (SES) for residents, and greater population density and ethnocultural diversity [48].

### Eligibility criteria

Study participants will be recruited from one hospital within each of the three sites. Each site aims to recruit 72 patients, yielding a sample size of 216 total participants. Older adult participants will be considered eligible if they meet the following criteria: 1) aged 65 years or older; 2) planned for discharge from hospital to the community (including private residences, retirement homes and transitional care beds); 3) self-report having a diagnosis of at least two chronic conditions; 4) self-report of having experienced depressive symptoms as assessed by a two-item version of the Patient Health Questionnaire (PHQ-2) [49]; 5) resides in one of the study regions and are not planning to move out of the region during the trial; 6) capable of providing informed consent or have a decision-maker who is able to provide informed consent; 7) is competent in English or has an interpreter who is competent in English (this also includes French-speaking individuals or French language interpreters at Site One). The adult caregiver(s) of trial participants, defined as family members or friends who assist with the management of their day-to-day activities by providing emotional, financial or other support, will also be invited to participate in the trial.

The Short Portable Mental Status Questionnaire (SPMSQ) [50] will be used to determine if eligible participants can provide informed consent (inclusion criterion 6). Participants will require a score of 5 or higher on the SPMSQ or have access to a substitute decision-maker. Individuals will be excluded from participation in the study if they are being discharged from hospital to a long-term care home, another hospital or hospital unit, or are not competent to provide informed consent and do not have access to a substitute decision maker.

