### Randomization and blinding

Within each study region, participants will be assigned to either the intervention or the usual care group following the collection of baseline data, using stratified permuted block randomization administered by a centralized web-based service (RedCap) to allocate clients at each site to the two groups in accordance with the sequence and using a 1:1 ratio. All study participants will be blinded to their group allocation (usual care or CAST intervention). Research assistants completing further assessments with participants following recruitment will remain blind to group assignments for the duration of data collection. Upon completion of the study at 12-months, participants will receive a mailed debriefing letter describing the two groups and their group allocation.

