Client-centredness of care	Adapted Client-Centred Care Questionnaire (CCCQ) [60]	PT, CG	T_1_, T_2_, and T_3_	-Descriptive analyses -T1: z test of proportions for group comparison, complete case analysis -T2: z test of proportions for group comparison, complete case analysis
Care experience	Integrated Care Patient-Reported Experience Measures (IC-PREMs) [61]	PT, CG	T_1_, and T_2_	-Descriptive analyses -T1: z test of proportions for group comparison, complete case analysis -T2: z test of proportions for group comparison, complete case analysis
Unmet care needs	Unmet Care Needs questionnaire	PT, CG	T_1_, T_2_, and T_3_	-Descriptive analyses - T1: z test of proportions for group comparison, complete case analysis -T2: z test of proportions for group comparison, complete case analysis
Caregiver strain	Modified Caregiver Strain Index (CSI) [62]	CG	T_1_, T_2_, and T_3_	-Descriptive analyses -T1-T2 (Treatment Effect): ANCOVA, complete case analysis -T2-T3 (Sustainability): ANCOVA, complete case analysis
Utilization of health and social services and associated costs	Institute for Clinical Evaluative Sciences (IC/ES), Health and Social Services Utilization Inventory (HSSUI) [63, 64]	PT, CG	T_1_, T_2_, and T_3_	-Descriptive analyses -T1-T2 (Treatment Effect): Mann-Whitney U test, complete case analysis, Hazard Ratio (95% CI) & Risk Difference (95% CI) for 30, 90 &180-day ED visits and hospital admissions -T2-T3 (Sustainability): Mann-Whitney U test, complete case analysis

*PT = patient; CG = caregiver, *T1 = baseline; T2 = 6-month; T3 = 12 months

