#### Analysis: effectiveness evaluation

Descriptive statistics will be used to summarize outcome values at baseline, 6 months and 12 months. Means and standard deviations will be used for continuous outcomes, and frequency and percentages will be used for categorical outcomes. Intention-to-treat analyses using analysis of covariance (ANCOVA) will be used to assess group differences in continuous outcomes from baseline to T2 in order to determine if the intervention was effective over the intervention period. The outcomes include: PRQ-2000, CESD-10, GAD-7, VR-12 PCS, VR-12 MCS, the PPC, CCCQ, and the IC-PREMs. The ANCOVA model will use the 6-month outcome value as the dependent variable, the group indicator as the independent variable and the baseline outcome value as the covariate. Model results will be expressed as mean group differences with accompanying 95% confidence limits. Quantile regression will also be used to examine the treatment effect over a broader range of values (beyond the mean) for the outcome variables. Assessment of group differences in continuous outcomes from T_2_ to T_3_ will be assessed using ANCOVA and will be aimed at assessing the sustainability of the intervention effects (see Table 1).

Z tests of proportions and McNemar tests will be used to assess changes within each group in the number of participants with acute care episodes and the number of acute care episodes from baseline to T_2_, and from T_2_ to T_3_ Acute care episodes include emergency department visits and hospital admissions. Risk difference (intervention risk – control risk) and accompanying 95% confidence limits will be calculated for 6 months for emergency department visits and hospital readmissions for 6 months. As was noted earlier, acute care episodes will be identified using administrative data from IC/ES, and self-reported data from the HSSUI. Due to the highly skewed nature of cost data, a non-parametric test will be used to compare the change in health and social service use and costs from baseline to T_2_ and from T_2_ to T_3_ for the two groups. Outliers are particularly common for certain healthcare costs such as hospital admissions, thus we will conduct a sensitivity analysis to assess the impact of outliers on the cost comparison.

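### The entry rule permits more than one caregiver per patient, but the analyses named for caregiver outcomes have no term for caregivers who share a patient (minor)

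*Protocol article*

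**What the plan says.** Under Eligibility criteria, the article describes who counts as a caregiver: "The adult caregiver(s) of trial participants, defined as family members or friends who assist with the management of their day-to-day activities", through emotional, financial or other support. These people "will also be invited to participate in the trial". No other caregiver entry rule is given. There is no maximum per patient, no definition of a primary caregiver and no expected number of caregivers.

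Under Randomization and blinding, allocation is at patient level: "Within each study region, participants will be assigned to either the intervention or the usual care group following the collection of baseline data", "using a 1:1 ratio". A caregiver's arm is therefore the arm of the patient.

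Under Analysis: effectiveness evaluation, the ANCOVA is specified with "the 6-month outcome value as the dependent variable, the group indicator as the independent variable and the baseline outcome value as the covariate".

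Table 1 marks ten of its eleven outcome rows as applying to caregivers; social support is the exception. The methods named in those ten rows are:

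- ANCOVA for VR-12 mental and physical scores, CESD-10, GAD-7 and caregiver strain. The strain row, which is for caregivers only, reads "T1-T2 (Treatment Effect): ANCOVA, complete case analysis -T2-T3 (Sustainability): ANCOVA, complete case analysis".
- z tests of proportions for the four experience and unmet-need measures.
- Mann-Whitney tests for service use and cost.

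No section mentions a random effect, generalised estimating equations, a cluster-robust variance or any other allowance for caregivers of the same patient.

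**The concern.** The entry definition is broad enough for a spouse, an adult child and a friend of one patient all to qualify. If two of them enrol, they share the patient's allocation, the patient's clinical course and, in the intervention arm, the same nurse coordinator. Their outcomes are then likely to be positively correlated even after each person's own baseline value is taken into account. ANCOVA with group and baseline alone, the z test and the Mann-Whitney test all take observations as independent. Applied to such data they count correlated caregivers as separate information, and patients with two caregivers weigh twice.

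At stake are the precision and false-positive rate of the caregiver comparisons (strain, depressive symptoms, anxiety, health-related quality of life, care experience, service use and cost). The first research question names caregivers alongside patients, so these results will be reported and interpreted.

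**Working it through.** **The plan's own figure.** The only sample size stated is for patients: 216, from a difference of 6.5, SD 15.0, power 80%, alpha 0.05 and 20% attrition.

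- Normal approximation: n per arm = 2 × (1.960 + 0.842)² × 15.0² / 6.5² = 83.6, rounded up to 84. The total is 168, and 168 / 0.80 = 210.
- t-based: 84.6, rounded up to 85 per arm. Then 85 / 0.80 = 106.25, rounded up to 107 per arm, or 214 in total.
- The next multiple of three sites above 214 is 216, which is 72 per site.

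The figure reproduces. It concerns patients only and does not depend on this point. No caregiver sample size or power is stated.

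**Inputs for the caregiver check.** Neither of the following is in the article, so both are assumptions shown over a range:

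- q, the share of patients with a caregiver who have two enrolled (none has more than two);
- ρ, the within-patient correlation of caregiver outcomes after baseline adjustment.

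The 0.05 level is from the article; two-sidedness is assumed.

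**Formulae.** With m caregivers per patient, E[m] = 1 + q and E[m²] = (1 − q) + 4q = 1 + 3q.

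- Design effect: DE = 1 + (E[m²]/E[m] − 1) × ρ = 1 + [2q/(1 + q)] × ρ
- True standard error / unadjusted standard error = √DE
- True two-sided error = 2 × [1 − Φ(1.96/√DE)]

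**Worked case, q = 20% and ρ = 0.3.** 2 × 0.2/1.2 = 0.333, so DE = 1 + 0.333 × 0.3 = 1.10 and √DE = 1.049. The error is 2 × [1 − Φ(1.96/1.049)] = 0.062.

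**Results.**

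| q | ρ | DE | √DE | True error at nominal 0.05 |
|---|---|---|---|---|
| 0% | any | 1.000 | 1.000 | 0.050 |
| 5% | 0.3 | 1.029 | 1.014 | 0.053 |
| 5% | 0.5 | 1.048 | 1.024 | 0.056 |
| 10% | 0.3 | 1.055 | 1.027 | 0.056 |
| 10% | 0.5 | 1.091 | 1.044 | 0.061 |
| 20% | 0.3 | 1.100 | 1.049 | 0.062 |
| 20% | 0.5 | 1.167 | 1.080 | 0.070 |
| 50% | 0.5 | 1.333 | 1.155 | 0.090 |
| 100% | 0.5 | 1.500 | 1.225 | 0.110 |

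Up to q = 20%, correct intervals would be at most 8% wider than the unadjusted ones. At ρ = 0.5, an error of 0.09 needs half of the patients with a caregiver to have two, and 0.11 needs all of them to. The formula is a normal approximation for a comparison of means. It applies most directly to the ANCOVA rows and is indicative for the proportion and rank tests.

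**The case against.** The strongest reply has four parts.

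1. **The plural may be only grammatical.** Beside a plural word for participants, a bracketed plural on caregiver need not mean several per patient. This stands in part. The wording permits several caregivers but does not show that any patient will have more than one enrolled.

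2. **Caregivers are not described as units.** A reader might infer that the plan treats each caregiver as an independent randomised unit. The article does not say so: it randomises patients and never describes caregivers as randomised. The independence assumption is inferred from the tests named. The list of ANCOVA outcomes in the text also includes the patient-only social support scale and omits caregiver strain, so it seems written mainly with patients in mind. That inference is nevertheless fair, because Table 1 assigns ANCOVA, z tests and Mann-Whitney tests to caregiver rows with no allowance for clustering.

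3. **The article is condensed.** The full protocol or the statistical analysis plan may fix one caregiver per patient or a clustered variance. That is possible and limits how firmly the point can be put. It does not remove the point, because the article does state an entry rule and does name methods, and the methods do not fit all the data that the rule allows.

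4. **The effect may be small or nil.** This stands fully. With one caregiver per patient there is no error. The correlation that matters is the residual one after baseline adjustment, which may be lower than a raw correlation.

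**Conclusion.** The point holds as a conditional mismatch of minor weight. The entry rule allows caregivers to be clustered within patients, and the named caregiver analyses do not account for it. It is tempting to conclude that the caregiver intervals are too narrow. The article does not support that as a statement of fact, because it requires that some patients have more than one enrolled caregiver, that the residual correlation is positive and that the analysis is run as named.

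With 0 to 20% of patients having two caregivers and a correlation of 0.3 to 0.5, the true error is 0.050 to 0.070 instead of 0.05. Both quantities are assumptions without a source in the article. Figures such as 0.110 describe an extreme case and should not be taken as the expected size.

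The consequence is confined to caregiver secondary outcomes. The primary analysis of the patient's VR-12 mental component score, the other patient outcomes and the sample size of 216 are untouched.

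**What to change.** State that caregiver outcomes will be analysed with the patient as the cluster:

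- cluster-robust standard errors or a random patient effect in the ANCOVA;
- cluster-adjusted versions of the proportion and rank tests, for example by resampling whole patients.

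If few patients have two caregivers, cluster-robust standard errors are the safer choice, since a random-effect variance would then be poorly estimated.

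Alternatively, if the sponsor intends one caregiver per patient, say so and have that person identified before randomisation, so that the choice cannot depend on the arm. Restricting entry in this way is a design preference and is not needed to solve the statistical problem.

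The cost is one sentence and a clustering option in the model, with slightly wider caregiver intervals. If every patient turns out to have one caregiver, the clustered analysis changes little. Under the one-caregiver alternative, data from any second caregiver would not be used.
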